## Data collection

Data collection will be performed by each hospital using an electronic data collection system designed specifically for the study. The filling will be done by each center based on data from medical records, according to local availability, respecting the maximum period of completion of two years. All data collected will be anonymous, in order to preserve the identity of the participants and guarantee confidentiality. The data to be collected are:

1. Charlson Comorbidity Index )
2. Reason for admission: Scheduled versus unscheduled. Presence of infection as the cause of hospital admission (defined as admission with a primary diagnosis of infectious pathology by ICD 10).
3. Physiological variables: Blood pressure, heart rate, respiratory rate, level of consciousness.
4. Laboratory variables: Renal function (serum creatinine), blood count, C-reactive protein (if available), coagulogram , bilirubin, serum lactate .
5. Result of all cultures (blood, tracheal secretion, urine or other sites) collected during hospitalization.
6. Length of stay in hospital
7. Use of intra-hospital resources

- a. Number of imaging tests performed to elucidate an infectious focus
- b. Need for surgical procedures
- c. Intensive care stay
- d. Use of supportive therapy such as mechanical ventilation, renal replacement therapy, use of vasopressors.

Laboratory and physiological variables will be collected from admission and during the first three days of the patient's hospitalization. In the event of addition, initiation or change of antimicrobial regimen and/or collection of some type of microbiological examination (culture), we will perform physiological and laboratory data collection again for an additional period of three days before and after the date of your occurrence. in order to monitor the occurrence of organic dysfunction associated with a suspected infectious condition (sepsis). In these situations, we will also note:

1. The causative focus of sepsis
2. The antibiotic prescribed and its suitability (i.e., whether the antibiotic prescribed at the initial time was effective against the pathogen that eventually proved to be the cause of the event )
3. Whether or not the infection was associated with a surgical procedure or invasive device (prosthesis infection, catheter-related bloodstream infection, etc. ).

We will also note the occurrence of other clinical complications, such as:

1. Pulmonary thromboembolism

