## **Statistical analysis**

Traditional univariate analysis comparing groups (case and control) with respect to the variables described above will be performed using t-test or Mann-Whitney test for continuous variables (as appropriate depending on the occurrence of normality) and Chi-square test for comparison of proportions.

The following approach will be used to calculate attributable fraction calculation for each admission type: The inverted probability weights (IPW) for each patient will be calculated, representing the cumulative risk of the patient acquiring sepsis during hospitalization, under a multivariable logistic regression analysis including baseline age, Charlson Comorbidity Index, and a time-dependent variable for the occurrence of clinically relevant events. We will estimate the association between sepsis occurrence on hospital mortality within 28 days through a mixed logistic regression model weighted by IPW. The model will include the participant center as a random intercept, and age, Charlson Comorbidity Index, infection at admission, IPW, and the accumulated dependent time variables of sepsis occurrence and clinically relevant events with their interaction with time (modeled with a third-degree polynomial). From the daily odds ratios

estimated by the model, the Miettinen formula will be used to calculate the attributable mortality of sepsis:

$$P_{c_i} * \frac{OR_i - 1}{OR_i}$$

*i = day,  $P_c$  = proportion of patients that had sepsis among non – survivors*

We will also present the marginal effect of having one sepsis episode on the whole period, with an estimate of average attributable fraction obtained from the model. All analyses will be performed using the R software

*Sensitivity analysis:* Different definitions of sepsis will be explored; the same analysis method described above will be used for different definitions as sensitivity analyses. An internal consensus was created within the steering committee on probability degrees of sepsis according to combinations of use of antibiotics, organ failure, results of cultures, and occurrence of clinically relevant events. Two sensitivity analyses will be made, one estimating the attributable fraction considering definitive, very probable, and probable sepsis, and a second sensitivity analysis considering only definitive and very probable sepsis.

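### Neither the weight model nor the outcome model names an admission vital sign or laboratory value, so acute severity at arrival is only crudely controlled in the sepsis-attributable fraction

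*Protocol*

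**What the plan says.** The text at issue is the second protocol text in the file, which carries the inverse-probability-weighting (IPW) plan.

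- **Weight model** (Statistical analysis): the weights are estimated "under a multivariable logistic regression analysis including baseline age, Charlson Comorbidity Index, and a time-dependent variable for the occurrence of clinically relevant events".
- **Outcome model** (same section): "The model will include the participant center as a random intercept", and the fixed terms are "age, Charlson Comorbidity Index, infection at admission, IPW, and the accumulated dependent time variables of sepsis occurrence and clinically relevant events", with interactions with time.
- **Stratification** (same section): the approach is used to "calculate attributable fraction calculation for each admission type". Data collection records admission type as scheduled or unscheduled.
- **Data available** (Data collection): "Physiological variables: Blood pressure, heart rate, respiratory rate, level of consciousness"; and "Laboratory variables: Renal function (serum creatinine), blood count, C-reactive protein (if available"), followed by coagulogram, bilirubin and lactate. On timing: "Laboratory and physiological variables will be collected from admission and during the first three days". The same list has "Presence of infection as the cause of hospital admission".
- **Sensitivity analyses** (Statistical analysis): there are two, and both vary only how certain the sepsis diagnosis must be.

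**The concern.** Cases are deaths and controls are live discharges, paired on date and time of discharge within a hospital. The two groups will differ in how ill they were on arrival, and nothing in the sampling removes that difference, so the models have to. Age and the Charlson index describe chronic risk. They say little about shock, reduced consciousness or renal failure at the door.

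Acute severity plausibly leads to nosocomial sepsis through longer stay, intensive care and devices, and it leads to death directly. The exposure definition may strengthen the link. Most of its eight organ-dysfunction criteria are thresholds to be met when antimicrobials are started or changed, with no requirement that the dysfunction be new. A patient who arrived with high creatinine or low platelets may therefore already meet the dysfunction part of the definition.

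The odds ratio goes straight into the Miettinen formula, Pc × (OR − 1)/OR. Any upward bias in it becomes deaths attributed to sepsis, in a figure that the Introduction says is meant to guide investment decisions.

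**Working it through.** **1. The plan's own figure.** Sample size section: 15% sepsis in controls, odds ratio 1.4, power above 90%, two-tailed. Alpha is not stated; 0.05 is assumed. Allocation is 1:1.

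- Odds in cases = 1.4 × 0.15/0.85 = 0.247, so the proportion in cases = 0.247/1.247 = 0.198.
- The two-proportion formula with continuity correction gives 1,345 per group, or 2,690 in total, against the stated 2,700. The figure reproduces, and this point does not affect it.
- The attributable fraction implied at the design values is 0.198 × 0.4/1.4 = 5.7%. This is a useful yardstick below.

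**2. Covariates side by side.**

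| Variable | Collected | Weight model | Outcome model |
|---|---|---|---|
| Age, Charlson | yes | yes | yes |
| Clinically relevant events | yes, as named complications | yes | yes |
| Infection at admission | yes | no | yes |
| Centre | yes | no | yes (random intercept) |
| Admission type | yes | by stratum | by stratum |
| Vital signs, consciousness | yes | **no** | **no** |
| Creatinine, blood count, bilirubin, lactate, coagulation | yes | **no** | **no** |

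Only the last two rows are missing from both models.

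**3. Bias factor by hand.** All inputs are assumptions. Let p0 be the prevalence of severe illness at arrival among patients without sepsis, k the odds ratio linking severity to sepsis, and R the risk ratio of severity for death. Then p1 = k·p0/(k·p0 + 1 − p0), and the bias factor is (R·p1 + 1 − p1)/(R·p0 + 1 − p0).

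| p0 | k | R | p1 | Bias factor |
|---|---|---|---|---|
| 0.20 | 2 | 2 | 0.333 | 1.333/1.2 = 1.11 |
| 0.20 | 2 | 3 | 0.333 | 1.667/1.4 = 1.19 |
| 0.10 | 3 | 4 | 0.250 | 1.75/1.3 = 1.35 |
| 0.20 | 3 | 4 | 0.429 | 2.286/1.6 = 1.43 |

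**4. Large-sample simulation of the plan's structure.** Assumptions: severity prevalence 30%; the same odds ratio from severity to sepsis and from severity to death (1.5, 2 or 3); infection at admission in 20% of patients without severity and 40% with it; one continuous score standing for age and Charlson; 1:1 case-control sampling; stabilised weights from that score alone; weighted logistic outcome model with the score and infection at admission. There is one time point and no centre, admission-type or clinical-events term.

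| Severity OR | True OR | As planned | Severity in both models | AF as planned | AF with severity |
|---|---|---|---|---|---|
| 1.5 | 1.0 | 1.05 | 0.99 | 0.6% | about 0 |
| 2 | 1.0 | 1.13 | 1.01 | 2.0% | about 0 |
| 3 | 1.0 | 1.31 | 0.99 | 5.1% | about 0 |
| 1.5 | 1.4 | 1.48 | 1.42 | 6.0% | 5.5% |
| 2 | 1.4 | 1.57 | 1.41 | 7.8% | 6.2% |
| 3 | 1.4 | 1.84 | 1.42 | 12.4% | 8.0% |

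In the strongest of these settings the spurious attributable fraction under no effect (5.1%) is close to the 5.7% implied by the design. In the weakest it is 0.6%.

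**5. Infection at admission in the weights.** Adding it to the weight model when it is already in the outcome model changes the odds ratio by at most 0.005 in the same simulations (for example 1.570 against 1.571).

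**The case against.** Several points on the other side stand.

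- A reader might infer from the three-term weight model that infection at admission and centre go unadjusted. They do not: both are in the weighted outcome model, and step 5 shows that repeating infection at admission in the weights matters little.
- A reader might also infer that acuity is wholly uncontrolled. The documents do not support that. Calculation by admission type separates scheduled from unscheduled patients, and the clinical-events variable is in both models. Its content is not fully defined, so how much acuity it captures is unknown. The word introducing the weight-model list also need not mean that the list is closed, though no other covariate is named.
- No severity association comes from the documents. The hand calculation treats severity as unrelated to everything the plan adjusts for; any correlation would shrink the residual bias. It is also static, whereas the plan models daily odds ratios.
- The direction is likely but not certain. The sickest patients may die before nosocomial sepsis can occur, which would weaken or reverse the link between severity and sepsis.
- Collection follows local availability, so complete first-day values cannot be assumed for every patient. Oxygenation and urine output, two of the inputs to the eight dysfunction criteria, are not in the listed physiological and laboratory variables, so a full eight-item count cannot be promised from that list.

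The other protocol text in the file based a marginal structural model on the physiological and laboratory variables. Departing from it is not an error, and the point does not rest on it.

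None of this puts a measure of physiological severity into either model, and neither sensitivity analysis would show the effect of leaving it out.

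**Conclusion.** The point holds in a limited form. Both covariate lists are written out, and neither contains an admission vital sign or laboratory value that the study collects. Acute severity at arrival is therefore incompletely controlled in the primary attributable fraction.

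The expected bias is upward, provided sicker arrivals are likelier both to acquire sepsis and to die. Under the assumed ranges a null effect would appear as about 1.05 to 1.4, and with a true odds ratio of 1.4 the attributable fraction would be 0.6 to 4.4 percentage points too high. These are illustrations of a plausible range. A reader might conclude that the bias is shown to equal the effect the study was sized for; only the strongest assumed scenario (1.43) reaches that.

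**What to change.** Pre-specify a baseline severity measure and enter it in both the weight model and the outcome model. Report the attributable fraction with and without it.

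- Build it only from listed variables: blood pressure, heart rate, respiratory rate, consciousness, creatinine, platelets (from the blood count), bilirubin, lactate and coagulation.
- Use first-day values taken before sepsis onset. Several of the same variables define organ dysfunction in the exposure, so later values would adjust away part of it. The eligibility criterion of a stay longer than 24 hours means every included patient has a first day to draw on.
- State how day-one dysfunction is handled in patients admitted with infection, where it may be sepsis already present.
- Infection at admission and centre may be added to the weight model for consistency; little should change.

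**Cost.** This is a change of analysis wording, with no new data collection. Values missing from charts, probably more often in less sick patients, need multiple imputation or a missing-indicator rule. The weights may become somewhat more variable, so their distribution should be reported.

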| Primary Purpose                   | To measure attributable mortality from nosocomial sepsis in hospitalized patients in Brazil.                                                                                                                                                                                                                                                                                                                           |
| secondary objectives              | 
 
1. Assess length of hospital stay in patients with or without sepsis
 
2. Assess mortality attributable to other hospitalization complications (infarction, stroke, pulmonary thromboembolism )
 
3. Evaluate the quality of completion of medical records
 
4. Assess the quality and consistency of filling in the hospital death certificate
 
 |
| Eligibility of cases and controls | Each hospital will provide clinical, demographic and laboratory data for the last 50 deaths that occurred in the institution. Data from the patient who was discharged alive with a date and time closer to the date of death of the case will be used as controls.                                                                                                                                                    |
| sample size                       | 30 hospitals, 100 patients in each hospital (50 cases and 50 controls), totaling 3,000 patients                                                                                                                                                                                                                                                                                                                        |

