## Eligibility criteria for patients

### Inclusion criteria

Each hospital will provide clinical, demographic and laboratory data for the last 50 deaths that occurred in the institution. Data from the patient who was discharged alive with a date and time closer to the date of death of the case will be used as controls. Fifty controls will be used per hospital, totaling 100 patients per hospital. Consecutive matching with the closest live high will ensure that any temporal impacts are minimized.

In addition to the general criteria mentioned, the specific inclusion criteria are:

- Patients over 18 years of age;
- Hospital stay for more than 24 hours;

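### A centre random intercept does not account for the fixed 50:50 sampling within each hospital and can leave the sepsis odds ratio too near 1

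*Protocol*

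**What the plan says.** The synopsis sets the sample as "30 hospitals, 100 patients in each hospital (50 cases and 50 controls), totaling 3,000 patients". Under Inclusion criteria, "Each hospital will provide clinical, demographic and laboratory data for the last 50 deaths that occurred in the institution", and "Fifty controls will be used per hospital, totaling 100 patients per hospital". Each control is chosen in relation to a case: "Data from the patient who was discharged alive with a date and time closer to the date of death of the case will be used". Cases and controls are therefore matched one to one within hospital, and also on calendar time.

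The Statistical analysis section (the one with the inverse-probability-weighted model) then analyses "hospital mortality within 28 days through a mixed logistic regression model weighted by IPW". On centre it states: "The model will include the participant center as a random intercept". It names no fixed centre term, centre stratification, conditional likelihood or matched-set term. The model is run separately by admission type ("The following approach will be used to calculate attributable fraction calculation for each admission type") and is time-dependent, with "accumulated dependent time variables of sepsis occurrence and clinically relevant events with their interaction with time". Its daily odds ratios go into the Miettinen formula, Pc × (OR-1)/OR, which gives the primary result.

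**The concern.** In a cohort, a centre random intercept describes how mortality differs between hospitals. Here the sampling has fixed the ratio of deaths to survivors in every hospital, so the observed data carry little or no such variation for the intercept to pick up.

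The quota also ties each hospital's intercept to its sepsis prevalence. If sepsis raises the odds of death and the hospital must still show 50 deaths in 100, the odds of death among its patients without sepsis have to be lower where sepsis is commoner. The random intercept assumes no such link.

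When a matching factor related to exposure is not conditioned on, the odds ratio is pulled toward 1. More patients do not remove this. Pc is an observed proportion, so an error in the odds ratio passes straight into the attributable fraction, while readers would believe that centre had been adjusted for.

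**Working it through.** **Inputs from the protocol.** 30 hospitals with 50 cases and 50 controls each; 15% nosocomial sepsis in controls and an odds ratio of 1.4 (Sample size).

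**Assumed, because the protocol gives no value.** The between-hospital SD of sepsis prevalence on the logit scale: 0, 0.5 or 1.0. With a centre value of 15%, the middle 80% of hospitals run from about 9% to 25% at SD 0.5 and from about 5% to 39% at SD 1.0. A true odds ratio of 3 is added to show a stronger effect.

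**The plan's own figure.** Sepsis in cases at OR 1.4: 0.15/0.85 × 1.4 = 0.2471, and 0.2471/1.2471 = 0.198. For 15% against 19.8%, two-sided 5% (alpha assumed), 90% power and continuity correction, the total is 2,690. The stated 2,700 is reproduced. This point does not affect it.

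**Step 1: the intercept depends on sepsis prevalence.** Let p0 and p1 be sepsis prevalence in a hospital's controls and cases. With equal numbers of each, the odds of death among patients without sepsis are (1-p1)/(1-p0). Take two illustrative hospitals with p0 of 5% and 30% and a true OR of 3:
- p0 = 5%: p1 = 13.6%, odds 0.864/0.95 = 0.91.
- p0 = 30%: p1 = 56.3%, odds 0.4375/0.70 = 0.63.

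The intercept falls as sepsis rises. Pooling the two hospitals gives mean p1 = 34.9% and mean p0 = 17.5%, so the crude OR is 2.53 although it is 3 in each.

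**Step 2: large-sample crude odds ratio over a distribution of hospitals.** Average p0 and p1 over the logit-normal distribution and form p1(1-p0)/[p0(1-p1)]:

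| True OR | Logit SD | mean p0 | mean p1 | crude OR | (OR-1)/OR, true | (OR-1)/OR, crude | reduction |
|---|---|---|---|---|---|---|---|
| 1.4 | 0 | 0.150 | 0.198 | 1.40 | 0.286 | 0.286 | 0% |
| 1.4 | 0.5 | 0.161 | 0.209 | 1.38 | 0.286 | 0.277 | 3% |
| 1.4 | 1.0 | 0.189 | 0.237 | 1.34 | 0.286 | 0.252 | 12% |
| 3 | 0 | 0.150 | 0.346 | 3.00 | 0.667 | 0.667 | 0% |
| 3 | 0.5 | 0.161 | 0.354 | 2.86 | 0.667 | 0.651 | 2% |
| 3 | 1.0 | 0.189 | 0.371 | 2.54 | 0.667 | 0.607 | 9% |

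Multiplied by Pc (mean p1), the attributable fraction at OR 1.4 goes from 6.0% to 5.8% (SD 0.5) or from 6.8% to 6.0% (SD 1.0). At OR 3 it goes from 23.6% to 23.0%, or from 24.7% to 22.5%.

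**Step 3: the random-intercept model gives the crude answer in this setting.** The model was fitted by maximum likelihood to simulated 30 × 50/50 data. For true ORs of 1.4 and 3 and logit SD up to 1.0, the estimated centre SD was about zero in every run and the OR equalled the crude one. At OR 1.4 it was 1.39 (SD 0.5) and 1.35 (SD 1.0), against 1.41 and 1.40 with a centre-stratified Mantel-Haenszel estimate. At OR 3 it was 2.90 and 2.54, against 3.03 and 2.96.

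**Step 4: features closer to the planned model.**
- One admission type only, OR 1.4: median centre SD 0.12 to 0.15; OR 1.42 against 1.43 stratified at SD 0.5, and 1.39 against 1.40 at SD 1.0. A separate run at OR 3 and SD 1.0 gave 2.54 against 2.98.
- 28-day death: centre SD near zero in 95-100% of runs if the share of late deaths varies little between hospitals; median 0.24 if it varies widely.
- Patient-day rows, OR 1.4 at patient level (the daily odds ratio is on another scale): with unequal stays, 2.70 and 2.74 against 2.75 at SD 0.5, and 2.77 against 2.91 and 2.93 against 3.00 at SD 1.0. With equal stays, 2.66 against 2.74 and 2.67 against 2.94.
- The inverse-probability weights were not simulated.

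**The case against.** The strongest objection is that the simplified model is not the planned one. Splitting by admission type, counting only deaths within 28 days, weighting, and using daily rows all disturb the exact 50:50 balance per hospital. Step 4 shows that the centre variance can then be clearly above zero and that in several settings the shortfall is slight. This stands. A reader might infer that the centre variance must collapse to zero and that the model becomes the crude analysis. The documents do not support that for the model as written. It can fail even at patient level: with a true OR of 5 and SD 1.0 the median centre SD was 0.17, although the OR was still 4.24 against 5.00 stratified.

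A reader might also infer that the attributable fraction will certainly be understated. The bias needs sepsis prevalence to differ between hospitals, the protocol gives no spread, and with none the bias is zero. At the design OR of 1.4 the shift is also well within the sampling error of a single study of this size (SE of the log OR about 0.09 to 0.10 in the same simplified setting).

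Neither point rescues the random intercept. None of these features makes it represent the quota, and every comparison with spread in Step 4 fell on the same side, toward 1. A systematic error in a known direction is not excused by being smaller than the sampling error.

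**Conclusion.** The point holds as a mismatch between sampling and model: hospital is a matching factor with a fixed case:control ratio, and a random intercept does not condition on it. The sepsis odds ratio and the Miettinen fraction can be biased toward the null, with an estimated centre variance that is often near zero.

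The size is conditional. In an unweighted patient-level model with 15% sepsis in controls, (OR-1)/OR is lower by nothing without spread, by about 2-3% at logit SD 0.5, and by about 9-12% at SD 1.0. The spread is assumed throughout, and the full model may show a smaller bias. The figures are a range under stated assumptions, not a forecast of this study's error.

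**What to change.** In the Statistical analysis section, replace the random intercept by centre as a fixed stratum in the primary model: either centre indicators or a logistic model conditional on centre. State in advance how sparse centre-by-admission-type cells will be pooled or merged.

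The change is about one sentence of wording. Precision falls modestly. In the simplified setting at OR 1.4, the SE of the log OR rose from 0.093 to 0.096 at SD 0.5 (about 4%) and from 0.086 to 0.098 at SD 1.0 (about 14%); up to roughly 15-20% should be allowed for. There are 100 patients per hospital overall but fewer within each admission type, hence the merging rule. Conditioning on centre does not deal with the matching on discharge date, which is a separate matter.

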## Study objectives

*Primary:* To measure attributable mortality from nosocomial sepsis in hospitalized patients in Brazil.

*Secondary:*

1. Length of hospital stay in patients with or without sepsis
2. To assess mortality attributable to other hospitalization complications (infarction, stroke, pulmonary thromboembolism )
3. Evaluate the quality of completion of medical records
4. Assess the quality and consistency of filling in the hospital death certificate

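### The primary mortality model uses the IPW both as weight and as covariate and re-enters accumulated clinical events, which can move the sepsis odds ratio from a total towards a direct effect

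*Protocol*

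**What the plan says.** The Protocol file holds two successive protocol texts. This point concerns the Statistical analysis section of the second, which is treated as current.

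- **Weights.** They are described as "representing the cumulative risk of the patient acquiring sepsis during hospitalization" and are estimated "under a multivariable logistic regression analysis including baseline age, Charlson Comorbidity Index, and a time-dependent variable for the occurrence of clinically relevant events".
- **Outcome model.** Hospital mortality within 28 days is modelled "through a mixed logistic regression model weighted by IPW", with centre as a random intercept. Besides age and the Charlson index, the covariates are "infection at admission, IPW, and the accumulated dependent time variables of sepsis occurrence and clinically relevant events with their interaction with time", with time as a cubic polynomial.
- **Use of the result.** From the daily odds ratios, "the Miettinen formula will be used to calculate the attributable mortality of sepsis". The whole-period result is "an estimate of average attributable fraction obtained from the model". Both sensitivity analyses on the definition of sepsis repeat the same method.
- **Target.** The primary objective is "To measure attributable mortality from nosocomial sepsis in hospitalized patients in Brazil". The Introduction explains this as the rise in mortality that sepsis produces, and proposes it for projecting the benefit of measures that prevent sepsis.

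**The concern.** Two features of the covariate list conflict with the purpose of the weights.

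**Events.** Time-dependent weights are used so that variables which both predict sepsis and may result from it need not be conditioned on in the outcome model. Here the events are in the weight model and are then conditioned on anyway. A variable that accumulates over the stay, with no cut-off at sepsis onset, includes events after sepsis. Deaths that sepsis causes through those events are then not credited to sepsis.

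**IPW.** An inverse probability weight is a function of the patient's own sepsis history. Once it has done its work as a weight it has no role as a covariate, and holding it fixed while sepsis changes is close to a contradiction if the weight is unstabilised.

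At stake is the primary estimate. The daily fractions, the average fraction and both sensitivity analyses all come from this one model. The whole-period marginal effect is no escape: setting sepsis to absent while leaving a septic patient's IPW and later events as observed is not a no-sepsis counterfactual.

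**Working it through.** **1. The plan's own figure.** The only computed figure is the sample size. With 15% exposure in controls and OR 1.4, exposure in cases is 0.15 x 1.4 / (0.85 + 0.15 x 1.4) = 0.21/1.06 = 0.198. At 90% power and two-sided alpha 0.05 (assumed; not stated), the total is 2,608 without and 2,690 with continuity correction, against 2,700 stated. It is reproduced, and the present point does not depend on it.

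**2. Structure.** Let A be sepsis to date and L accumulated events.
- Unstabilised weight on day t: W = 1 / product over days s up to t of P(A_s = observed | past A, age, Charlson, L).
- Stabilised weight: SW = the same product with L left out, divided by the product with L included.

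W depends directly on whether and when the patient became septic. In SW most of that dependence cancels. The section mentions neither stabilisation nor truncation.

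**3. Simulation of the event problem.** All parameters are assumptions, because the protocol gives none: 28 days of person-day data, pooled logistic death model with cubic time, four replicates of 40,000 patients per scenario, direct sepsis log OR 0.5 (OR 1.65), event-to-death log OR 1.0. The sepsis-to-event log OR is set to 0, 1 or 2. There is no centre effect, sepsis-by-time term or case-control sampling.

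| Sepsis-to-event log OR | Total-effect OR | SW as weight only | SW + IPW covariate | SW + events | Plan's structure with W (weight and covariate, + events) |
|---|---|---|---|---|---|
| 0 | 1.61 | 1.64 | 1.60 | 1.65 | 1.58 |
| 1 | 1.84 | 1.81 | 1.75 | 1.65 | 1.59 |
| 2 | 2.12 | 2.18 | 2.12 | 1.69 | 1.66 |

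The total effect rises down the table. Both event-adjusted columns stay near the direct effect, whichever weight is used.

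**4. Effect on the attributable fraction.** The fraction is Pc x (OR-1)/OR, so at a given Pc it changes in proportion to (OR-1)/OR. Total effect against the plan's structure:
- log OR 0: 0.377 against 0.367, within simulation noise.
- log OR 1: 0.456 against 0.372.
- log OR 2: 0.528 against 0.397; 0.397/0.528 = 0.75, a quarter lost.

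A separate simulation, with sepsis tripling the odds of an event and the event tripling the odds of death, gave less. The OR fell from 3.1-3.3 to 2.9, so the factor went from 0.68-0.70 to 0.66, a relative loss of 3-6%.

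**5. IPW as covariate.**
- *Stabilised.* The OR goes from 1.635 to 1.603, 1.805 to 1.753 and 2.179 to 2.117: changes of 2.0%, 2.9% and 2.8%.
- *Unstabilised.* The correlation of W with sepsis status is about 0.9 (0.88 in the separate simulation, where the median weight was about 99 on septic days and 1.02 on others). With events also in the model and the outcome model correctly specified, the main cost is precision: the Monte Carlo standard error of the mean log OR rises from about 0.02 to 0.04-0.08.
- *Unstabilised and misspecified.* With a quadratic Charlson effect left out of the fitted models and no mediation, the plan's structure gives 0.80 against a true 1.82. SW as weight only gives 1.86. Adding effect heterogeneity and mediation, the figures are 1.15, 2.36 and 2.41.

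**The case against.** **The events are neither defined nor dated.** That some follow sepsis is an inference, and if sepsis does not raise later events nothing is lost (first row of the table). This stands as a limit on size. It does not remove the fault, because the stated rule accumulates events with no cut-off at sepsis onset.

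**The target may not be a total effect.** The Introduction also speaks of separating sepsis deaths from those due to accompanying problems or to other cause groups, which could justify adjusting for cardiovascular events. This has some force. But the same Introduction defines the quantity as the mortality increase produced by sepsis and uses it to project the effect of preventing sepsis, and no direct-effect estimand is declared.

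**Events are confounders, and secondary objective 2 needs them.** Confounding by events is already handled in the weight model. Mortality attributable to infarction, stroke and thromboembolism calls for its own models; it is no reason to condition the sepsis estimate on them.

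**The IPW may be meant as a risk score, or stabilised in an unseen SAP.** If it is a risk score, weighting by it is not inverse probability weighting, and the sentence still needs correcting. If it is stabilised, the covariate does little harm, and this is conceded.

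**A stronger reading.** A reader might infer that the sepsis coefficient is neither a total effect nor interpretable. The documents do not support that. In one simulation, adding the IPW alone gave an OR of 8.2, or 148 on the log scale, but those figures need unstabilised weights, and the second also a log transform; the protocol states neither. A spread of 0.84 to 2.16 for the full structure in 1,500 + 1,500 samples has no matching target value and cannot be set against the cohort figure of 3.1-3.3.

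**Conclusion.** The fault is in a stated rule, not in a detail left open. The model conditions on events that may follow sepsis and on a function of the exposure, and it supplies every attributable fraction in the current plan.

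- **Events.** The odds ratio moves from the total towards a direct effect under either type of weight. The loss in (OR-1)/OR runs from almost nothing to 0.53 falling to 0.40. The upper end needs an assumed sepsis-to-event log OR of 2 (OR about 7.4); the true value is not in the documents.
- **IPW covariate.** It serves no purpose. The effect is about 3% of the OR at most if stabilised. If unstabilised, it loses precision, with possible bias in either direction when the outcome model is misspecified.

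The direction of the event problem follows from the text, given that sepsis raises the risk of at least some later events that themselves raise mortality. Its size cannot be fixed from the protocol. The correction should be made before the primary analysis is run.

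**What to change.** For the primary sepsis estimate:

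1. Use the IPW only as a weight, stabilised on the baseline covariates.
2. Remove the IPW, and the accumulated clinical events with their time interaction, from the outcome-model covariates.
3. Keep the events in the weight model only, lagged to before sepsis onset.
4. Keep age, Charlson index, infection at admission, centre, time, cumulative sepsis and sepsis-by-time in the outcome model.
5. Estimate mortality attributable to infarction, stroke and thromboembolism (secondary objective 2) in separate models.
6. If the event-adjusted model is of interest, keep it as a sensitivity analysis labelled as a direct effect.

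The cost is a short rewording of the section and a little more analysis work, because secondary objective 2 needs its own models. No new data are required and the sample size does not change.
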